## Discussion

Patients with postoperative adjuvant chemotherapy for gastric cancer have poor quality of life and heavy symptom burden. In clinical practice, there is no effective treatment to solve this problem. Acupuncture has been proven to be effective in improving side effects associated with various tumor treatments, and it is worth conducting large-scale clinical studies to clarify the efficacy of acupuncture in improving overall quality of life in these patients.

A sufficient acupuncture dose, especially the number of treatments, is important for the clinical effectiveness of acupuncture treatment for common conditions. Some studies reported that more acupuncture sessions appeared to be associated with better outcomes in patients with knee osteoarthritis and chronic pain [44, 45]. However, excessive acupuncture treatment may lead to increased medical resources, heavier traveling, and financial burden. The frequency of acupuncture in oncology settings varies from daily [46] to weekly [18] with huge heterogeneity in different countries and regions. In many Chinese studies, 2–3 times a week was the common choice for the frequency of acupuncture interventions [15, 47], whereas weekly acupuncture was more common in the US [18, 48]. The results of the pilot trial [27] showed a similar trend in quality of life scores between the high-dose and low-dose groups of acupuncture. In this full-scale trial, if the similarity between LA and HA groups is still observed, an equivalence study between high-dose and low-dose acupuncture will be worthy, considering the transportation, economic, and healthcare cost of high-dose acupuncture. Alternatively, if an obvious trend of differentiation is observed, then a differential study may be worth conducting to determine the appropriate dose of acupuncture.

This study will use AUCs as the primary endpoint instead of the scores at different time points during the postoperative adjuvant chemotherapy period to decrease heterogeneity. The AUC, as a standard metric in pharmacokinetic analyses, is often used for describing drug concentration. It also has been suggested as a preferred statistic in a variety of clinical settings [41, 42, 49, 50] for embracing all available information to interpret how much improvement after treatment, including evaluating pain relief and enhancement of sleep quality over time [51, 52]. The AUC provides relevant information on how much more improvement in HRQOL, on average, a patient may achieve with acupuncture therapy compared with usual care, rather than the scores at any specific time point.

This study continued to use an open-label design approach, considering the controversy about sham acupuncture control and the clinical meaning of acupuncture. Although sham-controlled trials with blinding are preferred from the perspective of methodology, trials without sham acupuncture have also been recommended recently, because of their emphasis on the practical applicability and increased external validity over treatment efficacy [53]. Sham acupuncture also has some limitations including latent ethics issues brought by unnecessary transportation costs for the sham acupuncture group, uncertain effect of inert control [54, 55], and the lack of consensus on approaches. For these reasons, more and more trials did not include a sham-acupuncture control group [48, 56]. We agree with the opinion of Molassiotis A. and colleagues that shifting the focus from placebo-related issues to those with clinical meanings is appropriate [57]. Although we did not use sham acupuncture in the pilot trial, the differences in quality of life between acupuncture and control groups are over the minimally important difference (MID) [35], indicating that this benefit is clinically meaningful. In addition, in order to control bias as much as possible, the statistician will be blinded to the treatment in this trial.

This study will be the first large-sample, multi-center randomized controlled trial on the efficacy of acupuncture on HRQOL and symptoms during postoperative adjuvant chemotherapy for gastric cancer. We are going to assess the effect of acupuncture, and to compare the difference between LA and HA groups on HRQOL in gastric cancer patients in a rigorous way by an adequately powered trial.

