**Discussion:**

This study aims to assess the effect of acupuncture and to compare the difference between LA and HA groups on HRQOL and symptom burden controlling in gastric cancer patients by an adequately powered trial.

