### Sample size

In our pilot trial, the total AUCs of FACT-Ga TOI during the 3 cycles of chemotherapy were 5402 and 4780 in the acupuncture and control groups, respectively, with a standardized derivation of 1109 [27]. Thus, a total of 62 participants will be needed in each arm to detect a significant difference between the control group and either LA or HA group, with an α of 0.025 and a power of 80%. Considering the total dropout rate of 22.41% in our pilot study and eliminating the impact of COVID-19 epidemics, we plan to enroll a total of 249 patients to allow a dropout rate of 25%.

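### The protocol calls the trial adequately powered to compare LA with HA, but its sample size calculation covers only acupuncture versus control

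*Protocol article*

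**What the plan says.** The end of the Background names two aims. Aim 1 is the effect of acupuncture on quality of life and symptoms. Aim 2 is the comparison of low-dose (LA) with high-dose (HA) acupuncture.

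The power claim appears twice. The abstract's Discussion names the assessment of acupuncture first, then states a further purpose: "to compare the difference between LA and HA groups on HRQOL and symptom burden controlling in gastric cancer patients by an adequately powered trial". The closing paragraph of the main Discussion promises "to compare the difference between LA and HA groups on HRQOL in gastric cancer patients in a rigorous way by an adequately powered trial". In both sentences the claim covers the dose comparison as well as the comparison with control.

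The Sample size section states what the number was chosen for: "62 participants will be needed in each arm to detect a significant difference between the control group and either LA or HA group". Its inputs are pilot mean AUCs of the FACT-Ga TOI that "were 5402 and 4780 in the acupuncture and control groups, respectively", an SD of 1109, an alpha of 0.025 and 80% power. Enrolment is set at 249 to allow for 25% dropout.

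On what the dose comparison might show, the Discussion reports that quality-of-life scores followed a similar trend in the two pilot dose groups. It adds that "if the similarity between LA and HA groups is still observed, an equivalence study between high-dose and low-dose acupuncture will be worthy", or, if the doses clearly separate, a study of their difference.

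**The concern.** The calculation takes one acupuncture mean and applies the same gain over control to LA and HA alike. It therefore contains no dose difference that could be powered. The abstract and Discussion nevertheless extend adequate power to the dose comparison, which is one of the two stated aims.

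What is at stake is how the dose result will be weighed. The Discussion makes the choice of the next study depend on whether the doses look similar or different. Someone told that the comparison was adequately powered could give a non-significant HA-LA result more weight than the design supports.

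This is a positive statement that the article's own Sample size section does not bear out. It is not a detail left to a fuller document.

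**Working it through.** **Inputs.** From Sample size: means 5402 and 4780, SD 1109, alpha 0.025, power 80%, 62 evaluable per arm, 25% dropout, 249 enrolled. From Statistical analysis: two-sided tests at 0.05, unadjusted LSD pairwise comparisons, baseline score as covariate. From Study design and Outcomes: 3 cycles of 21 days, so 63 days. The correlation between baseline score and AUC is not given; I assume r from 0 to 0.7.

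**Step 1: reproduce the plan's figure.**
- Difference: 5402 − 4780 = 622, or 622/63 = 9.9 TOI points averaged over the 63 days.
- Standardised effect: 622/1109 = 0.561.
- A two-sample t-test at two-sided 0.025 with 80% power needs 61.7 per arm, so 62.
- 62/0.75 = 82.7, so 83 per arm, and 3 × 83 = 249.

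The stated numbers reproduce. The calculation is sound for acupuncture versus control.

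**Step 2: what 62 per arm gives for HA versus LA, without baseline adjustment.**
- Standard error: 1109 × √(2/62) = 199.2.
- Normal approximation at two-sided 0.05 and 80% power: (1.96 + 0.84) × 199.2 ≈ 558. The t-test version gives 562.
- 562/622 = 0.90, and 562/63 = 8.9 TOI points averaged over 63 days.
- Power (t-test): 87% if the gap is the full 622, 64% at three quarters, 34% at half (311), 12% at a quarter.
- Detecting 311 with 80% power would need about 201 evaluable per arm, against 62 planned.

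**Step 3: allow for the planned analysis.** The full analysis set excludes, for lack of data, only patients with nothing after baseline, and missing scores are imputed. The number analysed may therefore approach 83 per arm. Baseline adjustment reduces the SD to 1109 × √(1 − r²). The results below are t-test based, at two-sided 0.05.

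| Per arm | Assumed r | Gap detectable with 80% power | Share of 622 | Power if gap is 311 |
|---|---|---|---|---|
| 62 | 0 | 562 | 90% | 34% |
| 62 | 0.5 | 487 | 78% | 43% |
| 62 | 0.7 | 402 | 65% | 58% |
| 83 | 0 | 485 | 78% | 43% |
| 83 | 0.5 | 420 | 68% | 54% |
| 83 | 0.7 | 346 | 56% | 71% |

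Testing at the 0.025 level of the Sample size section would be less favourable. With 62 per arm and r = 0, the detectable gap is 620 (essentially all of 622) and power at half is 24%.

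**The case against.** The strongest reply has three parts.

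1. **HA versus LA is not the primary comparison.** The abstract defines the primary outcome through the comparisons with control, and sizing a trial on its primary contrasts is normal practice. This stands. A missing power statement for Aim 2 would not be an error in itself; the error is only that adequate power is claimed for it.

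2. **The 90% figure is the unfavourable end.** It ignores the planned covariate and assumes that only 62 per arm are analysed. This also stands, and is why the range matters more than the single figure. The most favourable corner examined still gives 71% power for a gap of half the acupuncture effect.

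3. **The Discussion does not claim equivalence.** A reader might infer that a non-significant dose result will be taken to mean that low dose is as good as high dose, and that this trial should have set an equivalence margin. The document does not support either inference. Both outcomes it describes, similarity and separation, lead to a further study, and a margin belongs to that later trial. Nor can it be said that a null result is likely even if HA is clearly better. That depends on what gap counts as clear, and the article mentions a minimally important difference without giving its value. If the gap were the full 622, power would be 87% unadjusted with 62 per arm.

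**Conclusion.** The point holds as a correction to a stated property of the trial. Adequate power is shown for LA or HA versus control and is not shown for LA versus HA.

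Under the plan's own SD and two-sided 0.05 tests, the dose gap detectable with 80% power is 56% to 90% of the whole acupuncture-control effect, and power at half that effect is 34% to 71%. The upper figure of 90% rests on 62 analysed per arm without adjustment. The lower figure of 56% rests on all 83 per arm and an assumed baseline correlation of 0.7. The pilot's similar trend in the two dose groups gives no reason to expect a gap that large.

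The finding does not say that the sample size is wrong, since it is right for the comparison it names. Nor does it say that the plan draws an equivalence conclusion.

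**What to change.** In the abstract's Discussion and in the closing paragraph of the main Discussion, limit the claim of adequate power to acupuncture (LA or HA) versus control. Describe HA versus LA as a secondary estimation aim, reported as a baseline-adjusted difference in TOI AUC with its 95% confidence interval. In the Discussion paragraph on the follow-on study, say that the choice will rest on that interval and not on non-significance alone.

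The cost is that a claimed strength becomes less favourable. No patients are added, and the design and primary analysis are unchanged.

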## Data Availability

Not applicable.

## Abbreviations

HRQOL: Health-related quality of life
HA: High-dose acupuncture
LA: Low-dose acupuncture
FACT-Ga: Functional Assessment of Cancer Therapy-Gastric scale
PWB: Physical well being subscale of FACT-Ga
SWB: Social/family well being subscale of FACT-Ga
EWB: Emotional well being subscale of FACT-Ga
FWB: Functional well being subscale of FACT-Ga
GaCS: Gastric cancer subscale of FACT-Ga
TOI: Trial Outcome Index, composed of PWB subscale, FWB subscale, and GaCS subscale of the FACT-Ga Scoring
mESAS: Modified Edmonton Symptom Assessment Scale
AUC: Area under curve
AEs: Adverse events
SAEs: Severe adverse events
EDC: Electronic Data Capture
NCI-CTCAE: National cancer institute common terminology criteria for adverse events
